## DISCUSSION

The safety and efficacy of MMF in the treatment of LN have been tested in adults and in some pediatric subjects. However, data in both adults and children suggest that MMF_BSA_ does not reliably correlate with exposure to and subsequent immunological and clinical response to its biologically active metabolite, MPA [44]. Because of this weak correlation between MMF_BSA_ and MPA exposure, therapeutic drug monitoring presents a potential approach to optimize the use of MMF in pediatric LN.

The PLUMM study will provide high-level evidence that MMF_PK_ yields higher renal remission rates compared with MMF_BSA_ when used in the treatment of proliferative LN in cSLE. Currently, there are no controlled studies which provide a blinded, controlled head-to-head comparison of MMF_PK_ and MMF_BSA_ in either adult or pediatric LN. To the best of our knowledge, the PLUMM study is the first treatment trial in pediatric LN which is adequately powered.

We will collect data and biospecimens from 105 well-characterized pediatric LN patients, which will offer an unprecedented potential for collaborative ancillary studies. This will also allow for biobanking of DNA, RNA, plasma, and urine which will be used for supplementary studies of the pharmacogenetics (PG) of MPA. Future supplementary studies on MPA PG and the relationship of MPA with the pharmacology of hydroxychloroquine are anticipated to be successful, given the breadth of this study.

Additional strengths of the design of this study include a thorough evaluation of the pharmacokinetics of MMF in pediatric LN patients who are on concurrent medications, additional validation of a novel LN biomarker panel, and the testing of a novel SSR [34].

Notably, the SSR has been specifically developed for the PLUMM study in an international effort that used state-of-the art consensus methodology, statistical modeling, and true disease courses of children with LN. In brief, the SSR considers the time since LN diagnosis, the course of LN and extrarenal SLE, as well as the prior CS dosage since the preceding clinical assessment of the subject to suggest the dose of oral prednisone or IV methylprednisolone. Standardization of CS use is important, as CS are potent effect modifiers that require careful dosing in any randomized clinical trial of an inflammatory disease and has been identified to be one of the significant factors impacting the success of clinical trials in lupus [45,46]. This SSR is anticipated to manage and reduce variability of CS dosage using international consensus and real-life cSLE patient data.

The study design has some limitations. The feasibility of recruitment may be affected by the need in some patients for therapy with IV cyclophosphamide and/or B-cell depletion therapy (rituximab or belimumab). If such is deemed necessary for the treatment of a patient leading to their discontinuation of the study, their clinical outcome will still be monitored longitudinally. Concurrent use of calcineurin inhibitors may also affect MPA PK, so a subanalysis may be performed in those patients receiving this. Given the complex clinical course of cSLE patients, variability in CS dosing may persist despite SSR use, leading to potential deviation from the proposed standardized steroid regimen. If this was to be the case, then we will correct analyses for variation in CS dose and consider Bayesian analysis with causal interference strategies to correct for the CS effect. Since high doses of CS decrease exposure to MPA, we will repeat MPA PK measurement if a patient’s CS dose has changed by>50% or>20 mg since the last MPA PK profile. MPA PK may also be affected by concurrent medications. However, these will be kept stable during the study, other than CS.

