### Outcome measures and safety and efficacy endpoints

The primary efficacy outcome of the study is the improvement of proliferative LN as measured by the presence of at least PRR at the end of Part 1 of the study (week 26). The major secondary outcome is the achievement of CRR at the end of Part 1 of the study. Other secondary outcomes are the achievement of CRR at the end of Part 2 of the study (week 53) and frequency of adverse events defined as grade 3 or higher during all parts of the study using the National Cancer Institute Common Terminology Criteria for Adverse Events.

Exploratory outcomes include: change in Renal Activity Index for Lupus (RAIL) score (baseline visit to week 53) [23,24], rate of LN flares, time to PRR and CRR during the study (baseline visit to week 53), mean time-adjusted score of the Systemic Lupus Erythematosus Disease Activity Index (SLEDAI) [25], considering extra-renal domain items during the study (baseline visit to week 53), cumulative dose of oral corticosteroids (CS; in prednisone-equivalents) and cumulative exposure to intravenous CS during the study, frequency of patients fulfilling discontinuation criteria during the study, change in health-related quality of life as measured by the Pediatric Quality of Life Inventory (PedsQL) Generic Core Scale [26], during the study, percentage of patients with intake of ≥ 80% of prescribed MMF doses as per blister-pack count during the study, and presence of MPA-levels<0.1 mg/L from random testing or in-clinic testing during the study. The MPA primary and secondary outcome evaluations will be performed by independent blinded evaluators at the CCC, according to validated criteria. Outcome definitions are provided in Table 2.

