### Randomization

Eligible subjects enrolled in the study will be randomized (1:1) at baseline to receive either MMF_PK_ or MMF_BSA_. Randomization will be stratified by LN class (class 3 or 3/5 ***vs.*** class 4 or 4/5) as per the ISN/RPS and extrarenal manifestations of cSLE (extrarenal SLEDAI score<10 ***vs.*** ≥ 10). Race (white or non-white) and belimumab treatment (yes/no), as well as other important factors which have a known association with long-term outcomes of LN will be considered as potential confounders during the analyses. We will use variable block sizes to ensure balance and to minimize risk for unmasking. Thus, we will be using block sizes of 4 and 2 in random order.

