### Sample size and power estimation

The PLUMM study is the largest clinical trial in pediatric LN, to the best of our knowledge, which is adequately powered. Sample size was determined from a combination of prevalence data and precedents in the literature [13,14,35–43]. A sample size of 45 subjects per group with proliferative LN is anticipated to provide a power of 80% for the primary aim of detecting a significant difference in the rate of PRR between the MMF_PK_ and MMF_BSA_ arms at the end of Part 1, at a 2-sided 5% significance level by a two-group Chi-square test, assuming the rate of PRR is 55% in MMF_BSA_ and 83% in MMF_PK_. The sample size of 90 will ensure 81% of power to detect a statistically significantly difference in the rate of CRR between the two study arms, assuming a smaller proportion of 14% and a larger proportion of 43%. Based on the above presented power analyses, we will plan to enroll 105 subjects, to allow for up to 14.3% attrition rate during Part 1 of the study.

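### Correcting efficacy analyses for on-study corticosteroid dose would adjust the arm comparison for a consequence of treatment; the sentence should be limited to a labelled supplementary analysis

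*Protocol article*

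**What the plan says.** All references are to the protocol article.

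- **Discussion, limitations paragraph.** If CS dosing remains variable despite the SSR, "then we will correct analyses for variation in CS dose and consider Bayesian analysis with causal interference strategies to correct for the CS effect" (interference is presumably a slip for inference). The sentence does not say which analyses are meant or how much variation sets it off.
- **Discussion, on the SSR.** In recommending a dose, "the SSR considers the time since LN diagnosis, the course of LN and extrarenal SLE, as well as the prior CS dosage". The current course of nephritis therefore feeds into each CS dose.
- **Outcome measures and safety and efficacy endpoints.** The exploratory outcomes include "cumulative dose of oral corticosteroids" and cumulative intravenous CS exposure.
- **Standardized steroid regimen.** CS are described as strongly anti-inflammatory and able to influence the arm comparison, and so the primary outcome.
- **Discussion, limitations paragraph, again.** High CS doses lower mycophenolic acid exposure, and a large change in CS dose leads to a repeat pharmacokinetic measurement.
- **Statistical analysis.** The primary outcome is compared between arms by a method for a binomial outcome, with no CS term. Binary secondary outcomes follow the same approach.

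**The concern.** A covariate can safely enter a randomised comparison if it was fixed before randomisation. On-study CS dose was not. If one arm controls nephritis better, the SSR will tend to give that arm a different CS course. CS dose then lies downstream of both the randomised treatment and the developing response.

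Putting it in the model as a covariate does two things. It removes any part of the arm effect that shows up in CS dose. It also opens a path through the nephritis course, which drives both CS dose and the week-26 outcome, so randomisation no longer protects the estimate.

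There is a further link specific to this trial. CS alters mycophenolic acid exposure, and only the PK arm has its dose adjusted to exposure. Responding to CS-related changes in exposure is part of the strategy under test, so holding CS fixed can remove part of that contrast.

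The unrestricted word for what will be corrected, together with a trigger judged on trial data, leaves the reader unable to tell which result is confirmatory once CS variation has been seen.

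**Working it through.** **Step 1. The plan's own figures.** From Sample size and power estimation: 45 per arm, "assuming the rate of PRR is 55% in MMF_BSA_ and 83% in MMF_PK", tested "at a 2-sided 5% significance level by a two-group Chi-square test", stated power 80%. With Δ = 0.83 − 0.55 = 0.28 and pooled rate 0.69:

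power = Φ{[Δ√n − 1.96·√(2·0.69·0.31)] / √(0.55·0.45 + 0.83·0.17)} = Φ{[0.28·6.708 − 1.96·0.654] / 0.623} = Φ(0.957) = 83.1%.

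The stated 80% is slightly conservative for the named test: with a continuity correction the power is 76.3%, and by exact Fisher test 77.7%. The point does not depend on this. It fixes the reference values: 28 points and 83.1% power without a CS term.

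**Step 2. Is CS dose downstream of treatment?** Set side by side, the sections say that the SSR uses the nephritis course, that cumulative CS is an outcome, that CS affects the primary outcome, and that CS affects drug exposure. Each makes on-study CS a post-randomisation variable tied to treatment or response. None makes it a baseline confounder.

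**Step 3. Illustrative size.** The article gives no figure for how strongly CS dose follows nephritis course or how strongly CS improves response, so both are assumed and varied. Simulation of 400,000 subjects:

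- nephritis course when CS is set: I = m·d·arm + noise (variance 0.5)
- CS = −r·I + √(1 − r²)·noise (variance 0.5)
- final status: Y = I + (1 − m)·d·arm + b·CS + noise (variance 0.5)
- response if Y exceeds a cut-off; cut-off and d are calibrated to 55% and 83%.

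Here r is the link from nephritis course to CS dose, b the direct benefit of CS, and m the share of the arm effect already present when CS is set. Response is regressed (logistic) on arm and CS, then standardised to a risk difference. Approximate power puts the standardised rates into the Step 1 formula.

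| r | b | Adjusted difference in points (power), m = 0.5 | Same, m = 1 |
|---|---|---|---|
| 0 | 0 | 28.3 (84.1%) | 28.1 (83.3%) |
| 0.3 | 0 | 27.0 (80.2%) | 25.4 (75.1%) |
| 0.5 | 0 | 24.6 (72.5%) | 21.1 (58.8%) |
| 0.7 | 0 | 21.1 (58.7%) | 14.2 (30.8%) |
| 0.3 | 0.4 | 28.6 (84.7%) | 28.7 (84.9%) |
| 0.5 | 0.4 | 27.6 (82.0%) | 26.6 (79.0%) |
| 0.3 | 0.8 | 30.3 (88.5%) | 33.2 (93.6%) |
| 0.5 | 0.8 | 30.4 (88.8%) | 34.6 (95.3%) |

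The first row is a check: with no link, adjustment changes nothing. The unadjusted difference in the simulated sets ranged from 27.7 to 28.4 points, so tenths of a point should not be read. The difference shrinks when CS mainly marks poor response (b = 0) and grows when the direct CS benefit is large (b = 0.8). Higher power in the latter rows is no gain, because the quantity estimated has moved away from the 28 points that the strategy delivers.

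**The case against.** **The primary test has no CS term.** This is correct. A reader might infer that the randomised comparison will be replaced. The documents do not support that: Statistical analysis gives the primary and binary secondary comparisons without CS, and the Discussion sentence is conditional and could equally describe an additional analysis. What stands is that the sentence is not restricted to additional analyses, while Standardized steroid regimen frames the worry in terms of the primary outcome.

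**Thresholds and model details belong in the analysis plan, which is not shown.** Also fair; their absence alone would be no finding. The point is the commitment that is stated.

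**Causal methods are named.** A properly specified method for time-varying treatment could handle CS dose that is affected by earlier response. But it is only to be considered, alongside a correction that will be made.

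**The correction may concern departures from the SSR, not total dose.** Possible, and departures would follow response less directly. However, the article attributes the remaining variation to the complex clinical course of these patients, so departures too would be expected to follow disease.

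**Direction.** It is tempting to conclude that the correction must understate the PK effect. That follows only if CS has little effect of its own, and the article says that its effect is strong.

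**Belimumab.** A reader might extend the argument to "belimumab treatment (yes/no"), listed among potential confounders. The Randomization section names it beside race and does not say that on-study use is meant. The Discussion's remark on B-cell therapy concerns a need that leads to discontinuation, which is a different matter. The extension is not supported.

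**Conclusion.** The point holds in a limited form. The article commits to correcting unspecified analyses for a variable that is set after randomisation from the nephritis course, affects drug exposure and is listed as an outcome. Done by ordinary adjustment, this would not estimate the total effect of PK-guided against BSA-based dosing.

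Under the assumed links, 28 points becomes about 14 to 27 in the attenuating scenarios and about 29 to 35 in the opposite ones. Attenuation is the more plausible direction, because the SSR ties CS dose to the nephritis course, but the direction is not fixed. The simulation shows that the shift can matter in a trial planned at 80% power; it does not predict its size. The text leaves the primary comparison unprotected without saying that it will be changed. It should be corrected, and it is no fault in the primary test as written in Statistical analysis.

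**What to change.** Amend the limitations sentence in the Discussion, and the full protocol or analysis plan if it carries the same rule, to state that, whatever CS variation is observed:

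1. The primary and secondary efficacy comparisons stay as in Statistical analysis and adjust, if at all, only for pre-randomisation variables such as the stratification factors and baseline CS dose.
2. On-study CS dose is reported by arm, as the exploratory outcome it already is.
3. Any CS-corrected analysis is labelled supplementary, has its estimand stated, and uses a method for time-varying treatment affected by prior response (for example, a marginal structural model) in place of covariate adjustment.

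The cost is wording. Sample size, visits and treatment are unaffected. The supplementary analysis needs CS dose and nephritis measures over time; the coordinating centre already receives site data to issue its steroid recommendations. With 105 subjects, a weighted analysis of this kind may be imprecise, which is a further reason to keep it supplementary.

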## CONCLUSION

The PLUMM study is the first study of its kind to conduct a head-to-head comparison of pharmacokinetically-guided precision-dosing of MMF versus MMF dosed on body surface area, with respect to the achievement of renal disease remission in pediatric proliferative lupus nephritis. This study will yield high-quality evidence that will provide a foundation for leveraging therapeutic drug monitoring of MMF, thus leading to improved clinical outcomes in pediatric lupus nephritis.

## Figures and Tables

**Figure 1: F1:**
[figure not shown]
Pharmacokinetic pathway of MMF and MPA. Note: MMF-mycophenolate mofetil; MPA-mycophenolic acid; MPAG-MPA-glucuronide; CES-carboxylesterases; UGT-uridine 5’-diphospho-glucuronosyltransferases.

**Figure 2: F2:**
[figure not shown]
The PLUMM Study design. Note: R-randomization; MMF_BSA_-treatment arm of MMF dosed at 600 mg/m^2^ body surface area about 12 hours apart; MMF_PK_-treatment arm of MMF dosed twice daily to achieve an area under the concentration-time curve (AUC_0–12h_) of MPA ≥ 60–70 mg*h/L, CRR-complete renal response; PRR-partial renal response; NR-non-responder; CYC-cyclophosphamide.

**Table 1: T1:** Key eligibility criteria.

Key inclusion criteria	Key exclusion criteria
1. Age 8-<18 years at the time of enrollment	1. Presence of features (from SLE or other chronic disease) that a-priori suggests that the subject benefits from other therapies than that suggested or allowable by the study protocol.
2. New diagnosis with proliferative LN as per the ISN/RPS classification criteria [21], based on kidney biopsy done within 60 days of enrollment. For study inclusion, the kidney biopsy needs to be newly interpreted as one of the following classes: class 3, class 3/5, class 4, or class 4/5	2. History of significant kidney disease prior to the diagnosis of SLE
3. Diagnosis with cSLE [47,48], per the classification criteria of the ACR [49]/EULAR [50] (i.e., SLE with diagnosis prior to or at age 18 years)	3. Estimated GFR <40 mL/min/1.73 m^2^ using the modified Schwartz equation [55].
4. Tolerates MMF as per the treating physician	4. Need for renal replacement therapy at the time of enrollment
5. SLEDAI-R [25,51–54], score>0	5. CYC within 12 weeks of enrollment
	6. Anti-CD20 monoclonal antibody treatment within 6 months, except if CD19/20+ counts are normal by flow cytometry analysis)
	7. Specific blood dyscrasias

**Note:** LN-lupus nephritis; ISN/RPS-International Society of Nephrology/Renal Pathology Society; cSLE-childhood-onset systemic lupus erythematosus; ACR-American College of Rheumatology; EULAR-European League Against Rheumatism; MMF-mycophenolate mofetil; SLEDAI-R-renal domain score of Systemic Lupus Erythematosus Disease Activity Index; GFR-glomerular filtration rate; CYC-cyclophosphamide.

**Table 2: T2:** Definition of key efficacy measures.

Outcome measure	Definition	References
Partial renal remission	PRR is defined as relevant improvement of 2 LN-RV* with the remaining LN-RV being at least stable.	[22,34]
Complete renal remission	CRR is the presence of all 3 LN-RVs within normal range.	[22,34]
Lupus nephritis flare	A LN flare is the reproducible+ presence of 1 or more of the following (a-d) that is at least partially due to renal inflammation from LN per the treating physician. a. Newly abnormal GFR plus increase in hematuria by at least 2 categories (normal: 0 to 5 RBC/HPF (normal), 6 to 10 RBC/HPF, 11 to 25 RBC/HPF, 26 to 50 RBC/HPF, >50 RBC/HPF) OR new gross hematuria (>50 RBC/HPF). b. Abnormal GFR that decreased by >10% plus increase in hematuria by at least 2 categories (normal: 0 to 5 RBC/HPF (normal), 6 to 10 RBC/HPF, 11 to 25 RBC/HPF, 26 to 50 RBC/HPF, >50 RBC/HPF) OR new gross hematuria (>50 RBC/HPF). c. Persistent increase of UPCR to >0.5, after CRR d. Persistent doubling of UPCR with values >1.0, after PRR	[22,34]

**Note:** PRR-partial renal response; LN-RV-lupus nephritis core response variables; CRR-complete renal response; GFR-glomerular filtration rate; RBC/HPF-red blood cell per high-power field; UPCR-urine protein to creatinine ratio.

* LN-RVs are the upper limit of normal (ULN) or lower limit of normal (LLN) of the following:

Urine protein to creatinine ratio (ULN: 0.2), estimated GFR (LLN: 95 ml/min/1.73m^2^) and glomerular hematuria (ULN:0)

+ Reproducibility means presence on >2 subsequent time points >1 week apart.
